## Abstract

**Background:**

Agitation is prevalent among people with dementia (PWD) in nursing homes. It frustrates both the PWD and their caregivers. Acupressure is a non-pharmacological intervention whose effectiveness is supported by preliminary studies. However, there is still a dearth of evidence to explain its effect for clinical use and further research. The present study is being conducted primarily to investigate the effects of acupressure as compared with sham-acupressure and usual care.

**Methods/design:**

This study is a multicenter, assessor/participant/statistician-blinded, parallel group, randomized controlled trial taking place in Hong Kong nursing homes. We have been recruiting PWD over 65 years of age in nursing homes, who are experiencing agitation; 99 participants will be recruited in order to demonstrate a significant effect difference (that is, f =0.27) with a power of 0.8 and a significance level of 0.05 among the three groups. Participants are assigned by permuted block randomization into three groups in a 1:1:1 ratio. In the acupressure group, participants receive acupressure at the Fengchi (GB20), Baihui (GV20), Shenmen (HT7), Niguan (PC6) and Yingtang (EX-HN3) acupoints. In the sham-acupressure group, participants receive pressure on five non-acupoints. In the usual-care group, participants receive no intervention apart from the care provided by the nursing homes. Participants assigned to the sham-acupressure and usual-care groups receive free acupressure, like those in the acupressure group, after completion of the study. The whole study lasts for 30 weeks, and its primary outcome measure is agitation. The general estimated equation model will be used to compare the effects among groups and time points. The trial is currently recruiting participants.

**Discussion:**

This trial will provide a higher quality of evidence than previous studies on the use of acupressure for agitation in PWD. It will also provide newer evidence on acupressure in the population of PWD with agitation for clinical application and further research, including the effect on moderating stress, the delayed effect, the added effect on the placebo, and the effect on moderating the participant’s use of psychotropic drugs.

**Trial registration:**

Centre for Clinical Trials Clinical Trials Registry: CUHK_CCT00347 (Registration date: 13 December 2012).

## Background

Agitation is excessive, disruptive and inappropriate activities with verbal, vocal and motor components that are unexplained by apparent needs or confusion [1–3]. It can also be conceptualized as one of many behavioral or psychological symptoms of dementia [4] or as a neuropsychiatric symptom [5]. Agitation is the term most commonly used by professionals in long-term care facilities to describe dementia-related behavioral symptoms [6, 7]. Agitation is often the most prevalent neuropsychiatric symptom in residential care homes (RCHs), with prevalence ranging from 20.5% to 63% [8–11]. Agitation decreases quality of life [12, 13], and causes many negative consequences, such as falling [14] and use of restraints [15]. Agitation in PWD also increases caregivers’ burden [16, 17] and distresses formal caregivers [17, 18].

Acupressure is a non-pharmacological intervention whereby pressure is applied to specific acupoints on the body to treat a wide range of conditions or promote individual well-being [19]. It is a multi-modal therapy whose working mechanism can be explained by many different theories [20]. For example, traditional Chinese medicine (TCM) explains that acupressure stimulates the acupoints to enhance the energy or Qi flowing along the meridian, achieving therapeutic outcomes by improving the functions of body systems or Zangfu in the process [21]. Bio-chemical studies explain that stimulation of the acupoints by pressure may cause complex neuro-hormonal responses [22]. One of these responses may involve the hypothalamic-pituitary-adrenocortical axis to counteract the overproduction of cortisol and cause a relaxation response [23]. Similar manipulative therapies, such as massage and therapeutic touch, were shown to be useful in lowering the patient’s stress and cortisol after treatment [24, 25].

Preliminary studies [26–28] have shown that acupressure can reduce agitation in PWD. However, given that the participants and the RCH staff providing the outcome observation were not blinded in the previous studies, the extent of the placebo effect could not be estimated. Previous studies showed that manipulative therapies, such as massage [23, 29] and therapeutic touch [25, 30], had also reduced the agitation and stress of PWD. These studies led the present researchers to hypothesize that acupressure may produce an agitation-reducing effect by mediating the stress hormone (that is, cortisol) through tactile stimulation alone, instead of via acupoint stimulation. Many other factors that might account for the effect were not reported in previous studies, such as the delayed effect of the intervention and the use of psychotropic drugs.

Therefore, we designed the present study primarily to investigate the effectiveness of acupressure for reducing agitation, compared with sham-acupressure and usual care. Meanwhile, we further investigated the effect of acupressure on stress moderation (that is, reduction of cortisol level), the delayed effect, the efficacy of acupressure in addition to the placebo effect (that is, compared with the sham-acupressure), and whether acupressure leads to a reduction in psychotropic drug use.

## Methods/design

### Design

This study is a multi-center, assessor/participant/statistician-blinded, parallel group, randomized controlled trial. Participants are randomly allocated to three groups in a 1:1:1 ratio: the acupressure group, the sham-acupressure group, and the usual-care group. Eligible participants will be recruited from nursing homes in Hong Kong.

### Trial process

In order to recruit a sufficient number of participants in multiple nursing homes and balance the manpower demands, the whole study will be completed through six study cycles. The periods of each cycle partially overlap in order to efficiently utilize the manpower and study venues. Each study cycle lasts for 10 weeks, including a 2-week baseline period, a 2-week intervention period, and a 6-week follow-up period (Table 1). The whole study period lasts for 30 weeks.

**Table 1 Tab1:** **Trial process chart of each study cycle**

	Baseline	Treatment phase	Follow-up phase		
Tasks	Week -2	Week 0	Week 3	Week 5	Week 8
**Participants/next-of-kin**					
Informed consent	x				
Sign the proxy consent	x				
Obtain participant’s assent	x				
Access medical record	x				
Physical examination	x				
**Intervention**					
Acupressure group (n =33)		x			
**Control**					
Sham-acupressure group (n =33)		x			
Usual-care group (n =33)		x			
**Outcomes**					
Agitation (CMAI)		x	x	x	x
Stress (salivary cortisol)		x	x	x	x
**Monitoring**					
Compliance with the intervention		x			
Reasons for withdrawal		x	x	x	x
Adverse events/safety		x	x	x	x

*CMAI*, Cohen-Mansfield Agitation Inventory.

### Recruitment procedures

We have invited all the RCHs in Hong Kong that are registered under the Social Welfare Department and fulfill the following criteria: (1) they have more than 100 beds; and (2) they provide beds for moderate/severe functioning elders (that is, Care and Attention Homes and Nursing Homes) [31]. The RCHs are invited by mail and followed up by telephone. Of the RCHs who were interested in participating, 12 RCHs were selected randomly to launch this study. Only 12 were selected because it was estimated from the pilot study [32] that at least 12 RCHs with more than 100 beds each would provide sufficient participants for the study (that is, 99 participants). Within the 12 selected RCHs, our research team is working closely with RCH staff to screen all the residents against the selection criteria. After screening, all eligible residents are invited to participate in the study by telephone. Participants are included only if they meet the selection criteria and provide assent/informed consent, and if the next-of-kin provide written informed proxy consent (Figure 1).

**Figure 1 Fig1:**
[figure not shown]
**Trial flow chart.**

### Randomization

Permuted block randomization is used. The permuted block randomization list was generated by the web-based generator at http://www.randomization.com
[33]. To guarantee allocation concealment, randomization is done by an independent research assistant who does not participate in any other parts of the research. Throughout the study period, the independent research assistant generates the randomization list and keeps the list. Information on the recruited participant (for example, name, age, and gender) is sent to the independent research assistant by email after the recruitment. The independent research assistant assigns the group code to each participant according to the randomization list and sends the information back to the researcher by email. The independent research assistant is blinded to the meaning of the group code.

### Blinding

Participants, next-of-kin, data collectors, nursing home staff (that is, the formal caregivers providing the Cohen-Mansfield Agitation Inventory (CMAI) data and the nurses administering the psychotropic drugs), physicians prescribing the psychotropic drugs, and the statistician will be blinded to the group allocation status; however, blinding is clearly not possible in the usual-care group. The group allocation status will only be revealed after completion of the study.

### Participants

This study focuses on older nursing home residents with dementia and agitation. Eligible participants should match all the inclusion criteria, and participants meeting any of the exclusion criteria should be excluded.

#### Inclusion criteria

Participants will be included if they fulfill the following criteria: (1) aged over 65 years, (2) documented as having dementia in the medical record, and (3) identified as having agitated behaviors for the period 1 month prior to the time of recruitment according to the criteria for agitation stated in the Instruction Manual for CMAI [34].

#### Exclusion criteria

Exclusion criteria are: (1) skin problems on acupoints (for example, skin breakdown, infection), (2) musculo-skeletal problems (for example, amputation of the acupoints), and (3) having received acupuncture/acupressure within the 8 weeks immediately prior to the day of recruitment.

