#### Acupressure group

In this group, we use five acupoints: Fengchi (GB20), Baihui (GV20), Shenmen (HT7), Niguan (PC6) and Yingtang (EX-HN3). The researchers first identify the acupoints; the acupoint identification method in this study is based on two textbooks [38, 39] with complete agreement from the expert panel. The researchers then apply pressure on the acupoints, following a light-strong-light pattern. They increase the pressure gradually until it reaches the optimal level, sustain the pressure at the optimal level for 3 minutes, gradually decrease it after 3 minutes and finish by kneading the pressed acupoints. The optimal pressure is defined by experiencing the Deqi sensation (that is, soreness, numbness, distention, heaviness) [40]. The optimal pressure to achieve the Deqi sensation differs among individuals. The sensation can be confirmed by asking the participants and observing their behavior (for example, frowning, withdrawing). When the pressure increases to a level where the Deqi sensation begins to be obviously felt by the participants or observed by the interventionist, the level of pressure is regarded as optimal.

Yintang (EX-HN3) is first pressed for 3 minutes. Baihui (GV20) and Fengchi (GB20) are then pressed simultaneously for another 3 minutes. Finally, Neiguan (PC6) and Shenmen (HT7) are pressed simultaneously for the last 3 minutes. For the bilateral acupoints (that is, GB20, PC6, HT7), the acupoints on one side are pressed in each session and they are pressed alternatively along sessions. Each acupressure session lasts for 9 minutes. Acupressure is performed twice a day, 5 days a week (from Monday to Friday) for 2 weeks. A course of acupressure consists of 20 sessions and lasts for 2 weeks.

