#### Sham-acupressure group

In this group, five non-acupoints are used as controls. A non-acupoint is defined as a point on the body not falling on the acupoints depicted in the two TCM reference books [38, 39] and agreed by the members of the expert panel. The five non-acupoints are the root of the nasal bone (point 1), the olecranon of the ulna (point 2), the ulnar styloid process (point 3), the medial malleolus (point 4), and the head of the fibula (point 5). Pressure is applied on the five non-acupoints in the same way as in the AG. Point 1 is first pressed for 3 minutes. Points 2 and 3 are next pressed simultaneously for another 3 minutes. Finally, points 4 and 5 are pressed simultaneously for the last 3 minutes. For the bilateral points (that is, points 2, 3, 4, and 5), the points on one side are pressed in each session and they are pressed alternatively along sessions. The intervention dose and duration are the same as in the AG. The participants in this group receive a free course of acupressure sessions, identical to the one stipulated in the AG, after completing the study.

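### The skin exclusion covers acupoints only, although sham participants are pressed at five sites that are by definition not acupoints; the musculoskeletal exclusion is unclear on the same point

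*Protocol article*

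**What the plan says.** All places are in the protocol article.

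- **Exclusion criteria.** The first two criteria are "skin problems on acupoints (for example, skin breakdown, infection), (2) musculo-skeletal problems (for example, amputation of the acupoints"). The third concerns recent acupuncture or acupressure and does not matter here. Sham sites are not mentioned.
- **Acupressure group.** The points pressed are "Fengchi (GB20), Baihui (GV20), Shenmen (HT7), Niguan (PC6) and Yingtang (EX-HN3").
- **Sham-acupressure group.** "A non-acupoint is defined as a point on the body not falling on the acupoints depicted in the two TCM reference books". The sites are the nasal root, the olecranon, the ulnar styloid and "the medial malleolus (point 4), and the head of the fibula (point 5"). On technique: "Pressure is applied on the five non-acupoints in the same way as in the AG". Points 2 to 5 are bilateral; one side is pressed per session, and the sides alternate.
- **Table 1.** A physical examination is marked at Week -2. Its content is not described and it is not tied to any pressure site.
- **Analysis.** Both per-protocol and intention-to-treat analyses are planned. Receipt of more than 80% of sessions is given as an example of the per-protocol requirement.

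**The concern.** In a randomised comparison, eligibility should ensure that each person entered could receive any of the arms. Here the skin criterion does this for the acupressure sites and not for the sham sites. A resident with broken skin at the ankle meets no skin exclusion. In the acupressure or usual-care arm that skin problem has no bearing on treatment. In the sham arm the same resident may have sustained pressure on damaged skin, or may not receive the sessions.

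Two things are at stake. One is participant safety. The other is the acupressure-versus-sham contrast, which the Background and Discussion sections rely on to separate acupoint stimulation from touch alone. Non-delivery, withdrawal or loss from the per-protocol set that can arise in one arm only, after randomisation, weakens that contrast.

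**Working it through.** The plan states no figure on this point, so the main check is a comparison of texts. The arithmetic only gives scale.

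**1. Sites screened against sites pressed**

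| | Acupressure sites | Sham sites |
|---|---|---|
| Pressed in | Acupressure arm | Sham arm |
| Are they acupoints? | Yes | No, by the article's own definition |
| Covered by the skin exclusion | Yes | No |
| Covered by the musculoskeletal exclusion | Yes | Unclear: the criterion has no site limit, but its only example concerns acupoints |
| Pressure technique | Raised to the Deqi sensation, held for 3 minutes | The same |

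The word acupoints in the skin criterion might mean the five study points or all points in the two reference books. On either reading it excludes the sham sites, because these were chosen to lie off every acupoint in those books. No other section extends the screen to them.

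**2. How many sham participants might be affected**

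Inputs: 33 per group (Sample size estimation); prevalence p of an unscreened problem at a sham site, which the article does not give. The range 1% to 10% is an assumption.

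Expected number = 33p. Chance of at least one = 1 - (1 - p)^33.

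| Assumed p | Expected of 33 | Chance of at least one |
|---|---|---|
| 1% | 0.3 | 28% |
| 2% | 0.7 | 49% |
| 5% | 1.7 | 82% |
| 10% | 3.3 | 97% |

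**3. What one affected participant could lose**

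- A course is 2 sessions a day x 5 days x 2 weeks = 20 sessions.
- Sides alternate at points 2 to 5, so a problem on one side touches about 20/2 = 10 sessions.
- If those whole sessions are not given, 10/20 = 50% are received. This is below the example threshold of more than 80%, and the participant leaves the per-protocol set.
- If only the affected 3-minute step is dropped, the loss is 10 of 20 x 3 = 60 steps, or one sixth. Whether a session with a step left out counts as received is not stated, so the per-protocol consequence is possible but not certain.

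**The case against.** The strongest case against has five parts.

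1. **Musculoskeletal criterion.** A reader might infer that a resident with a leg amputation is eligible. The text does not support that. The criterion is musculoskeletal problems in general, and only the illustration mentions acupoints, so a broad reading excludes such a resident. This stands: the criterion is ambiguous, not limited to acupoints.
2. **Harm is not shown.** A reader might also infer that some sham participants cannot safely be treated. The article gives no prevalence and does not say what happens when a site is unsuitable. This stands: the text supports only that they may be unable to receive the allocated pressure.
3. **The effect may be small.** If only the affected step is dropped, even 10% prevalence costs 0.10 x 10/60 = 1.7% of the sham arm's pressing time. The intention-to-treat analysis keeps affected residents in their arm, and the sample size allows for 10% attrition. This stands in part. An attrition allowance protects power, not balance between arms. The Safety and adverse events section also removes participants with suspected adverse events from the study after discussion, so a problem at a sham site could cost follow-up data as well as sessions.
4. **Other safeguards.** Adverse events are monitored, undelivered intervention is recorded, and a baseline physical examination is scheduled. These would reveal a shortfall and limit its consequences. They do not extend eligibility to the sham sites.
5. **A condensed article.** Site-by-site screening detail may sit in a full protocol that is not shown. That lowers confidence that the sham sites went unchecked in practice. It does not remove the difficulty that the criterion as published names the sites of only one of the two pressure arms.

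**Conclusion.** The point holds in a limited form. As written, the skin exclusion omits every sham site and the musculoskeletal exclusion is ambiguous about them. A resident with a skin problem at a sham site can therefore be randomised to sham, with possible pressure on damaged skin, missed sessions, withdrawal or per-protocol exclusion in that arm alone.

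The textual gap is certain. Its size is not: 0.3 to 3.3 of 33 sham participants rests wholly on the assumed 1% to 10%, and loss from the per-protocol set depends on how an incomplete session is counted. No bias in the intention-to-treat estimate has been demonstrated, and its likely effect there is modest. The gap still deserves correction because it concerns participant safety and the comparability of the two pressure arms, and because closing it is cheap.

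**What to change.** Reconcile the Exclusion criteria section with the Sham-acupressure group section, so that skin and musculoskeletal eligibility is assessed at the acupressure and the sham sites on the same basis, on both sides where a site is bilateral. Do this for every candidate before randomisation. State whether the musculoskeletal criterion is general or tied to the pressure sites. Name the Week -2 physical examination in Table 1 as the occasion for the check. Which findings make a candidate unsuitable is for the investigators to define.

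The cost is a short wording change and slightly more screen failures; no new visit is needed. The article reports that recruitment is under way, so the change helps only participants not yet randomised. Record the date on which it takes effect.

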### Intervention

This intervention protocol was developed according to the 2008 Medical Research Council guideline for developing complex interventions [35]. The intervention was developed based on three methods: a literature review, the Delphi process [36] and a pilot study. The literature review [37] identified articles discussing the theories possibly connecting the use of acupressure and the agitation. Evidence relevant to the use of acupressure on agitation in PWD was retrieved by a systematic review from the major databases. The aim of the literature review was to identify the existing evidence and develop theories to explain why acupressure might work. The relevant information retrieved from the literature was then summarized as a document for the subsequent Delphi process. In the Delphi process [37], a panel of six TCM experts specializing in acupuncture was consulted. All TCM experts on the panel were TCM practitioners registered in either Hong Kong or mainland China with a bachelors degree or above. The expert panel has rich experience in practicing TCM and clinical acupuncture, with a median of over 15 years in practice. The Delphi process first asked the panel experts to suggest the intervention components (that is, the selection of acupoints), the intervention dosage, and the rationales for the selection of components. They were then asked to give suggestions with reference to the information provided in the literature and their own professional knowledge and experience. Finally, consensus on the procedural details of the intervention protocol was reached through three cycles of stepwise anonymous discussion until the content validity index achieved 1.0. Although consensus on the intervention dosage (that is, the duration and frequency) was reached in the Delphi process, the narrative comments from the Delphi process showed that the dosage was based on the experts’ experience only because TCM theory does not discuss dosage. A pilot study was performed to provide supporting evidence for the dosage selection. In the pilot study [32], within the range of dosage suggestions given in the Delphi process, the effect of acupressure was compared among various dosages. It was found that shorter duration with higher frequency showed a larger effect. The dosage that showed the largest and most significant effect was used in the intervention protocol, which is to conduct the intervention twice a day for 2 weeks.

#### Acupressure group

In this group, we use five acupoints: Fengchi (GB20), Baihui (GV20), Shenmen (HT7), Niguan (PC6) and Yingtang (EX-HN3). The researchers first identify the acupoints; the acupoint identification method in this study is based on two textbooks [38, 39] with complete agreement from the expert panel. The researchers then apply pressure on the acupoints, following a light-strong-light pattern. They increase the pressure gradually until it reaches the optimal level, sustain the pressure at the optimal level for 3 minutes, gradually decrease it after 3 minutes and finish by kneading the pressed acupoints. The optimal pressure is defined by experiencing the Deqi sensation (that is, soreness, numbness, distention, heaviness) [40]. The optimal pressure to achieve the Deqi sensation differs among individuals. The sensation can be confirmed by asking the participants and observing their behavior (for example, frowning, withdrawing). When the pressure increases to a level where the Deqi sensation begins to be obviously felt by the participants or observed by the interventionist, the level of pressure is regarded as optimal.

Yintang (EX-HN3) is first pressed for 3 minutes. Baihui (GV20) and Fengchi (GB20) are then pressed simultaneously for another 3 minutes. Finally, Neiguan (PC6) and Shenmen (HT7) are pressed simultaneously for the last 3 minutes. For the bilateral acupoints (that is, GB20, PC6, HT7), the acupoints on one side are pressed in each session and they are pressed alternatively along sessions. Each acupressure session lasts for 9 minutes. Acupressure is performed twice a day, 5 days a week (from Monday to Friday) for 2 weeks. A course of acupressure consists of 20 sessions and lasts for 2 weeks.

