#### Usual-care group

In this group, participants receive no acupressure-related intervention. They receive a free course of acupressure sessions, identical to the one stipulated in the AG, after completing the study.

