### Ethics review and informed consent

The study protocol was reviewed and approved by the Human Subjects Ethics Sub-committee of The Hong Kong Polytechnic University (HSEARS20120920001). In the recruitment phase, before the randomization, all the next-of-kin of subjects screened to be eligible are informed of the details of the study, including intervention and data collection procedures, potential risk and benefits. All eligible subjects are likewise informed of the same details. The subjects and the next-of-kin are clearly told about the equal chance of allocation to any one of the three groups before signing the informed consent. Subjects are recruited when 1) they sign the written informed consent (if they are sufficiently cognitively sound) or assent to participate (that is, nodding, verbalizing, or not rejecting when acupressure is performed on them), and 2) the next-of-kin sign the written proxy consent [42]. Due to the principle of blinding, only the participants allocated to the usual-care group will be told to wait for their free compensatory acupressure treatments after completion of the study. The group allocation status will be strictly concealed to the participants, next-of-kin, data collectors, and nursing home staff throughout the study period. The group allocation will only be revealed after completion of the study.

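### An observed withdrawal can by itself confirm Deqi and start a three-minute hold, even in a resident who cannot say whether it is sensation or refusal

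*Protocol article*

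**What the plan says.** The section on the acupressure group raises the pressure gradually until Deqi appears, and explains how to recognise it: "The sensation can be confirmed by asking the participants and observing their behavior (for example, frowning, withdrawing". The pressure counts as optimal once the sensation "begins to be obviously felt by the participants or observed by the interventionist". The interventionist is then to "sustain the pressure at the optimal level for 3 minutes" before easing off. Three such holds make up a session: "Each acupressure session lasts for 9 minutes".

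The sham section carries the technique over: "Pressure is applied on the five non-acupoints in the same way as in the AG". Sham and usual-care residents are later offered the real treatment. For usual care the article says: "They receive a free course of acupressure sessions, identical to the one stipulated in the AG, after completing the study". The sham section makes the same offer.

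Under ethics and consent, a resident who cannot sign may enter by assent, together with written proxy consent from the next-of-kin. The listed forms of assent are "nodding, verbalizing, or not rejecting when acupressure is performed on them".

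**The concern.** The same visible act can mean two opposite things. Under the intervention section, pulling away is a sign that the pressure has reached its target. Under the consent section, rejecting the pressing is a sign that the resident does not assent. A resident who can speak can settle which it is. For one who cannot, the intervention section is the only place that attaches an action to the sign, and that action is to hold the pressure.

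What is at stake is the welfare and continuing willingness of residents in the two pressed arms, and of those who take the free course afterwards. The treatment comparison itself is not in question.

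**Working it through.** The article gives no figure for this point, so the check is mainly a reading of the relevant sections side by side.

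1. **The sign.** Withdrawing is named as an example of behaviour that confirms Deqi (Acupressure group).
2. **Is observation enough?** The confirming sentence joins asking and observing with *and*. The sentence that defines optimal pressure joins felt and observed with *or*. The second sentence decides when the hold begins, so an observed sign suffices without any report from the resident.
3. **The action.** Once the pressure is optimal it is held for 3 minutes. The first sign therefore caps the force, but nothing in the stated sequence releases it.
4. **The arms.** The sham section applies pressure in the same manner, so both pressed arms follow the rule. The free course extends it to sham and usual-care residents after the study.
5. **The population.** Inclusion requires dementia documented in the medical record. Neither the inclusion nor the exclusion criteria set a cognitive or communication floor. The assent route exists for residents not able to sign. That some enrolled residents cannot report sensation is an inference from these two facts; the article gives no count.
6. **The competing meaning.** The consent section treats not rejecting the pressing as assent, so rejection counts against assent. The article does not say how to tell rejection from withdrawing.
7. **Do other stated safeguards settle it?** Proxy consent is obtained before randomization. The skill test was done on elderly volunteers and the trainer, and asked whether Deqi pressure was achieved. Suspected adverse events lead to exclusion after discussion among the team, home staff and family, which cannot act within a three-minute hold. None of these decides which meaning prevails.

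**What can be counted, and what it does not show.** Sessions: 2 per day x 5 days x 2 weeks = 20. Holds per session: 9 / 3 = 3. Holds per course: 3 x 20 = 60. This is all the pressing in a full course. It is not the number of holds in which a resident withdrew or could not report, so it is not the size of the problem.

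**Possible cost of the fix to the per-protocol set.** The article's example of adherence is more than 80% of sessions. 16/20 = 80% fails and 17/20 = 85% passes, so a fourth session counted as not received removes a resident. The article gives no rate at which sessions would be cut short. Assume that each session of a non-reporting resident is cut short independently with probability p and then counts as not received. The chance of four or more in 20 is:

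| assumed p | P(X >= 4), X ~ Binomial(20, p) |
|---|---|
| 0.05 | 1.6% |
| 0.10 | 13.3% |
| 0.20 | 58.9% |

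These figures describe the remedy under assumed rates, not harm from the present rule. Independence is doubtful because resistance probably clusters within residents.

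**The case against.** The best case for the plan has four parts.

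- **Withdrawing is not rejecting.** The article uses different words for a reaction at the onset of sensation and for dissent, and a brief flinch at Deqi may be legitimate. This stands. A reader might infer that the plan instructs staff to press on against refusal; no sentence says so. What remains is that the article offers no way to separate the two in a resident who cannot be asked.
- **The rule protects by capping.** Pressure rises gradually and stops rising at the first clear sign. This also stands, and it limits the force. It does not release someone who is pulling away.
- **The article condenses a fuller intervention protocol.** Handling of a resident who resists in mid-session may be set out there. That is fair, so the lack of a complete stopping procedure is not held against the plan. The point rests on the printed sentence that counts withdrawing as confirmation.
- **The assent wording is an entry condition.** It is introduced by "Subjects are recruited when 1) they sign the written informed consent", and the trial process chart places assent at baseline. A reader might infer that assent must be rechecked at every session; the article does not say that. The wording shows only that the investigators regard rejection of the pressing as meaningful.

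The surrounding oversight is real: ethics approval, adverse-event monitoring, monthly skill evaluation and a visit to each site. It does not govern what happens during a hold.

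**Conclusion.** The point holds in a limited form. As written, an observed withdrawal can by itself confirm Deqi and authorise a three-minute hold, in both pressed arms and in the free course. In a resident with dementia who cannot report sensation, that may answer a refusal with continued pressure. The conclusion rests on reading *or* in the definition of optimal pressure as it stands, and on the inference that some enrolled residents cannot report.

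The frequency is unknown. The documents give neither the number of such residents nor how often they withdraw, and nothing shows that the problem has occurred. A reader might take the 60 holds per course or the assumed stop rates as its size; neither measures it. Nor do the documents support any claim of bias, lost power or a changed error rate. This is an inexpensive improvement to participant safety, not a threat to the trial's validity.

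**What to change.** Amend the acupressure section, and through it the sham section and the free post-study course, to say three things:

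- Withdrawing stops any further increase in pressure.
- In a resident who cannot report sensation, withdrawing does not by itself confirm Deqi. Other signs, such as frowning, remain usable.
- If such a resident keeps pulling away, the hold is ended and noted on the compliance record that the trial process chart already provides for.

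The wording should be identical in both pressed arms. The intention-to-treat population is unaffected.

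The cost is a short amendment and a briefing for interventionists who have already been examined. The trial is recruiting in overlapping cycles, so delivery may differ slightly before and after the change, and its date should be recorded. Interventionists lose a little behavioural information for setting pressure in residents who cannot report. Some sessions will be recorded as incomplete, which may lower per-protocol numbers by an amount that cannot be stated in advance and that could differ between the acupressure and sham arms.
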